# High intensity interval training versus moderate intensity continuous training for people with interstitial lung disease: protocol for a randomised controlled trial

**DOI:** 10.1186/s12890-021-01704-2

**Published:** 2021-11-10

**Keywords:** Interstitial lung diseases, Idiopathic pulmonary fibrosis, Pulmonary Fibrosis, Exercise,, Rehabilitation, High-Intensity interval training, Endurance training

## Abstract

**Background:**

Interstitial lung disease is a debilitating condition associated with significant dyspnoea, fatigue, and poor exercise tolerance. Pulmonary rehabilitation is an effective and key intervention in people with interstitial lung disease. However, despite the best efforts of patients and clinicians, many of those who participate are not achieving clinically meaningful benefits. This assessor-blinded, multi-centre, randomised controlled trial aims to compare the clinical benefits of high intensity interval exercise training versus the standard pulmonary rehabilitation method of continuous training at moderate intensity in people with fibrotic interstitial lung disease.

**Methods:**

Eligible participants will be randomised to either a standard pulmonary rehabilitation group using moderate intensity continuous exercise training or high intensity interval exercise training. Participants in both groups will undertake an 8-week pulmonary rehabilitation program of twice-weekly supervised exercise training including aerobic (cycling) and strengthening exercises. In addition, participants in both groups will be prescribed a home exercise program.

Outcomes will be assessed at baseline, upon completion of the intervention and at six months following the intervention by a blinded assessor. The primary outcome is endurance time on a constant work rate test. Secondary outcomes are functional capacity (6-min walk distance), health-related quality of life (Chronic Respiratory Disease Questionnaire (CRQ), St George’s Respiratory Questionnaire idiopathic pulmonary fibrosis specific version (SGRQ-I), breathlessness (Dyspnoea 12, Modified Medical Research Council Dyspnoea Scale), fatigue (fatigue severity scale), anxiety (Hospital Anxiety and Depression Scale), physical activity level (GeneActiv), skeletal muscle changes (ultrasonography) and completion and adherence to pulmonary rehabilitation.

**Discussion:**

The standard exercise training strategies used in pulmonary rehabilitation may not provide an optimal exercise training stimulus for people with interstitial lung disease. This study will determine whether high intensity interval training can produce equivalent or even superior changes in exercise performance and symptoms. If high intensity interval training proves effective, it will provide an exercise training strategy that can readily be implemented into clinical practice for people with interstitial lung disease.

*Trial registration* ClinicalTrials.gov Registry (NCT03800914). Registered 11 January 2019, https://clinicaltrials.gov/ct2/show/NCT03800914

Australian New Zealand Clinical Trials Registry ACTRN12619000019101. Registered 9 January 2019, https://www.anzctr.org.au/Trial/Registration/TrialReview.aspx?id=376050&isReview=true

## Background

Interstitial lung disease (ILD) encompasses a large group of over 200 debilitating chronic lung conditions that share similar clinical, radiological, histopathological and pathogenetic features and are typically associated with chronic inflammation and fibrosis of lung tissue [1, 2]. Regardless of aetiology, people with ILD often suffer from dyspnoea, fatigue, anxiety, depression, cough, and reduced exercise tolerance. These symptoms are often debilitating and substantially affect health-related quality of life (HRQoL) [3, 4]. Fibrotic ILD (fILD) is a subset of patients where lung pathology is characterised by fibrosis [5, 6]. Some fibrotic ILDs are progressive and associated with a particularly poor prognosis, such as idiopathic pulmonary fibrosis (IPF), the most common and prototypical form of fILD [2]. Other ILD subtypes can develop a progressive fibrosing phenotype and have a similar clinical behaviour to IPF such as idiopathic nonspecific interstitial pneumonia (NSIP), unclassifiable idiopathic interstitial pneumonia (IIP), connective tissue ILD (CTD-ILD) (primarily rheumatoid arthritis (RA)-ILD), chronic hypersensitivity pneumonitis (HP), asbestosis and silicosis [1, 7, 8]. Fibrotic ILD represents a large portion of all ILDs, and people with fILDs typically have more profound dyspnoea, greater physical impairment and disability and a poorer prognosis than those with other types of ILD [1, 5, 7, 8].

There is an accumulation of robust evidence to indicate pulmonary rehabilitation (PR) is an effective and key intervention in ILD. A Cochrane review involving the meta-analysis of 22 randomised controlled trials (RCTs) of PR in ILD [9] found that PR significantly improved functional capacity, HRQoL and dyspnoea. These improvements are comparable in IPF and other ILDs, suggesting PR is effective regardless of aetiology [9]. In addition, current international guidelines support the inclusion of people with ILD in PR [10]. Despite this compelling evidence for the benefits of PR in ILD, the optimal exercise training strategy for people with ILD still needs to be explored. In our earlier RCT assessing the effectiveness of exercise training, utilising the standard PR method of continuous training at moderate intensity, in 142 people with ILD of varying aetiologies [11], less than half of the participants achieved a clinically meaningful improvement in 6-min walk distance (6MWD) following PR [12]. Furthermore, whilst benefits of PR were greatest in individuals who were able to progress the intensity and duration of their exercise training [11], successful progression occurred in only 40% of patients [13], the majority of whom had diagnoses other than IPF [13]. Therefore, current exercise training strategies in PR may not be well suited to people with ILD, particularly those with fILD such as IPF.

Impaired exercise tolerance is a well-known, prominent feature of ILD. In ILD, exercise intolerance is associated with gas exchange impairment and circulatory dysfunction. Probable causes include destruction and remodelling of the pulmonary-capillary vascular bed resulting in reduced diffusing capacity, ventilation perfusion mismatch and pulmonary hypertension. As consequence, people with ILD often present with arterial hypoxemia that worsens during exercise [14–16]. Skeletal muscle dysfunction also contributes to impaired exercise tolerance either due physical deconditioning, increased muscle oxidative stress, arterial hypoxaemia, systemic disease related manifestations and corticosteroids [16–20]. People with fILD tend to experience more severe diffusion limitation, greater exercise induced oxyhaemoglobin desaturation and have more severe pulmonary hypertension compared to those with other ILDs [14, 16, 21, 22]. Therefore, those with fILD often demonstrate a greater limitation to exercise and more profound exertional dyspnoea. These pathophysiological mechanisms of exercise limitation that are accentuated in fILD may limit patients’ ability to adhere to continuous training or to train at a high enough exercise intensity to achieve physiological benefits, therefore resulting in less favourable outcomes.

High intensity interval training (HIIT) may serve as an alternative exercise training regimen to the moderate intensity continuous training (MICT) method typically used in PR. High intensity interval training involves repeated intermittent bursts of high intensity exercise, interspersed by periods of rest or low-intensity exercise [23]. The exercise intervals may be performed at higher intensities than tolerated by continuous training, allowing for an increased training stimulus to peripheral muscles without overloading the cardiorespiratory system [23, 24].The alternating exercise and recovery bouts may also provide intermittent relief from the ventilatory demand of exercise [24], and may reduce the impact of circulatory dysfunction and gas exchange impairment that is often present in those with ILD [14–16]. High intensity interval training has been shown to be effective at improving cardiometabolic health across a range of populations including healthy individuals, people with diabetes, cardiac disease, and heart failure [23, 25, 26].

In chronic obstructive pulmonary disease (COPD), meta-analyses concluded HIIT was equally effective as continuous training in producing beneficial physiological change and improvement in HRQoL [27–29]. Additionally, in some studies HIIT was found to be associated with less leg discomfort [30–32], less dyspnoea [30–32] and greater adherence [33] when compared to continuous training. In ILD, there is little evidence on the benefit of HIIT. One small feasibility study comparing the efficacy of HIIT vs continuous training in ILD of varying aetiology provided preliminary evidence (n = 36) that HIIT is as effective as continuous training [34], although the duration of intervals varied among HIIT participants. Interestingly in their subgroup analysis, HIIT was found to be more effective in patients with IPF, although the sample size was small (approximately n = 12) [34]. This preliminary evidence suggests HIIT may be a more achievable method for people with fILD to attain the recommended exercise training intensity that promotes health-enhancing benefit. A robust, high quality trial is necessary to establish whether HIIT is an effective exercise training strategy in fILD.

The primary aim of this study is to compare the clinical benefits of HIIT vs MICT in people with fILD. We hypothesise that HIIT will deliver clinically significant improvements in exercise endurance (primary outcome), symptoms and HRQoL, which are superior to those achieved with the MICT method typically used in PR.

## Methods

### Design

A randomised, controlled, assessor-blinded trial comparing HIIT to the typical PR method of MICT will be conducted at four metropolitan sites in Australia (Alfred Health and Austin Health in Melbourne, The Prince Charles Hospital in Brisbane, and Royal Prince Alfred Hospital in Sydney). Participants with fILD will be randomized into two groups. Group 1: PR using the standard MICT method and Group 2: PR receiving HIIT. Participants will be followed up for six months following the completion of the allocated 8-week intervention. This six month follow-up period is clinically feasible in fILD without excessive loss to follow up due to transplantation or death [11, 35]. The study protocol (version 5, 19 March 2019) has been approved by the Alfred Hospital Human Research ethics committee with governance approval obtained from all participating sites (Alfred Hospital, Austin Hospital, Royal Prince Alfred Hospital and The Prince Charles Hospital). The study design follows the Standard Protocol Items: Recommendations for Interventional Trials (SPIRIT) checklist (see online supplemental file 1) [36]. The trial is registered at anzctr.org.au (ACTRN12619000019101) and ClinicalTrials.gov **(**NCT03800914).

### Participants

People with fILD who receive care at the participating sites will be invited to participate. Patients will be eligible for inclusion if they are (1) ≥ 18 years of age, (2) able to read and speak English and (3) have a physician-confirmed diagnosis of fILD via high-resolution computed tomography or histology such as IPF, CTD-ILD, HP, fibrotic NSIP, unclassifiable IIP, dust related lung disease or sarcoidosis. People with fILD make up a significant portion of all ILDs and are associated with a significant disease burden (5). Patients with these conditions may be unable to sustain MICT for long durations (15-30 min) possibly due to exertional dyspnoea and exercise induced desaturation [13].

Participants will be excluded if they have (1) a resting oxyhemoglobin saturation (SpO_2_) on room air < 85%; any absolute contraindication to performance of a cardiopulmonary exercise test (CPET) [37]; (2) severe pulmonary hypertension (mean pulmonary arterial pressure > 55 mmHg; World Health Organization (WHO) class IV); (3) attended PR within the last six months; (4) any comorbidities that would preclude exercise training or assessments; (5) a history of syncope on exertion; (6) significant cognitive impairment; (7) admission to an acute care hospital within the last 30 days or (8) if there is anticipated transplantation or death within the study period.

### Recruitment and randomisation

Potential participants will be identified by (1) their treating physician or ILD nurses when attending the respiratory medicine clinic or (2) when they are referred to PR program at the participating sites. Eligible participants will be provided with written and verbal information about the study from a clinician and/or a researcher. Patients will be informed that participation in the study is voluntary and their decision regarding participation will have no effect on their treatment, their relationship with their healthcare team or any other healthcare requirements. All participants will provide written informed consent.

Following the completion of the baseline assessments, patients will be randomly allocated to receive MICT or HIIT using a computer generated, permuted block randomisation scheme stratified for (i) SpO_2_ < or ≥ 90% during 6-min walk test (6MWT) on room air, to ensure that those who desaturate are evenly distributed between the intervention and control group, and (ii) site of recruitment. Sequence generation will be performed by an individual independent of the research team and the group allocation will be concealed using a secure online database. An independent assessor, blinded to group allocation, will perform the outcome assessments at each timepoint. Given the physical nature of the intervention (exercise training) participants will not be blinded to group allocation. The flow of participants through the study will be reported according to the recommendations from the Consolidated Standards of Reporting Trials statement [38] and is outlined in Fig. 1.

**Fig. 1 Fig1:**
[figure not shown]
Study Flow. 6MWT, 6-min walk test; HIIT, high intensity interval training; *MICT* moderate intensity continuous training; *PR* pulmonary rehabilitation; *SpO2* oxyhaemoglobin saturation

### Interventions

Participants in both groups will undergo a standard 8-week twice-weekly supervised PR at the centre where they were recruited. Each session will consist of lower limb aerobic training plus upper and lower limb resistance training exercises. The intensity (high versus moderate) and the type (continuous versus interval) of aerobic exercise training will differ between the two intervention groups.

#### Moderate intensity continuous training

Participants will perform 30 min of continuous aerobic exercise on a cycle ergometer each session. This can be completed in one or more bouts (e.g., 3 × 10 min, 2 × 15 min, or 1 × 30 min) as tolerated by the participant. The initial intensity of the stationary cycling will be set at the work rate equivalent to 60% of the peak work rate (Wpeak) achieved on the CPET [39, 40]. This approach represents the current standard practice for exercise training in PR programs for chronic lung disease [40–43].

#### High intensity interval training

Participants will perform 36 min of stationary cycling alternating 30-s exercise intervals at 100% of Wpeak achieved during a CPET, with 30 s unloaded pedalling or rest. Similarly, this can be performed in one or more bouts (e.g., 1 × 36 min, 2 × 18 min or 3 × 12 min) as tolerated by the participant. Informed by our pilot study, this interval format attenuated exertional desaturation and was associated with a similar symptom, oxygen consumption (VO_2_) and heart rate response when compared to moderate intensity continuous exercise [44] The volume of exercise, calculated as the product of exercise time and percentage of Wpeak, for HIIT which is 18 min at 100% Wpeak, is work-matched with the MICT volume of exercise of 30 min at 60% peak.

Exercise training and weekly progressions will be standardised across all sites. The intensity of cycle training will be progressed gradually over the 8-week period, as tolerated, based on patient symptoms, towards an overall 20% increase in work rate for both training groups. The resistance program for both groups will comprise at least two upper-body and two lower-body exercises, initially set at a load to achieve 8–12 repetitions for 2 sets of each exercise [41]. All participants will be encouraged to perform three additional unsupervised home-based sessions each week which will be documented in a home diary that is reviewed weekly by the supervising clinician. The home exercise sessions will include walking or cycling dependant on equipment availability and patient preference and strengthening activities utilising equipment readily available in the home environment. Supplemental oxygen will be provided during training if the participant is on long term and/or ambulatory oxygen therapy or if SpO_2_ on room air is less than 85% whilst exercising and is accompanied by symptoms and signs of severe hypoxemia. Supplemental oxygen will be used during home exercise in participants prescribed long term or ambulatory oxygen therapy.

### Outcome measures

Outcome measures will be collected at baseline, upon completion of the 8-week intervention period, and at six months follow up by an assessor who is blinded to the group allocation. At baseline, a symptom limited incremental cycle test (CPET) according to the international standardised protocol [37] will be performed (1) to establish a work rate for the constant work rate test (CWRT) and (2) to set the exercise training intensity for both groups at a percentage of the Wpeak. Data collection will also include age, sex, body mass index, past medical history, use of oxygen therapy, and current pharmacological treatment. Spirometry, completed as per usual care, will be collected at baseline and six months to document disease progression.

### Primary outcome

The primary outcome is change in endurance time measured using the CWRT on a cycle ergometer at 80% of Wpeak achieved on a baseline CPET according to the standardised criteria [37, 45, 46]. All tests will be performed on room air. The CWRT will be terminated before volitional symptom limitation if SpO_2_ < 78%. Endurance time is considered the most responsive outcome for evaluating exercise-related physiological changes following therapeutic interventions in COPD [45–47] and IPF [48].

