### Sample size

A total of 122 participants (61 per group) will be required to detect a clinically important difference between groups for the primary outcome measure of exercise endurance in the CWRT, with 80% power, and at the two-sided 5% level. This is based on the intermediate boundary (150 s) of the mean important difference range for the CWRT (SD = 292 s) [46, 68]. We will also be powered for the secondary outcome of HRQoL measured by the SGRQ-I based on data from our previous RCT of exercise training in ILD [11]. For HRQoL, a total of 114 participants are required to detect a mean difference of 6 points in SGRQ-I total score (SD = 11.3 points). In our previous trial, we had 5% attrition at completion of exercise training and 12% attrition at six months follow up [11]. Therefore, we will randomise a total of 130 participants, split evenly between groups.

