### Statistical analysis

Continuous outcome variables will be analysed using linear mixed models, controlling for recruitment site and baseline values as required. All data will be analysed by intention to treat, with inclusion of all available data regardless of whether the intervention is completed. The proportion of participants who completed the program, adhered to the exercise training protocol and had an adverse event will be compared between groups using a chi-squared test. Alpha will be set at 0.05.

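### The primary endurance time can be cut short by the SpO2 stop, and the article neither says which quantity it targets nor separates these stops in the one model it names

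*Protocol article*

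**What the plan says.** The Primary outcome section of the protocol article states: "The primary outcome is change in endurance time measured using the CWRT on a cycle ergometer at 80% of Wpeak" reached on the baseline incremental test. On test conditions it says: "All tests will be performed on room air". It then sets the early stop: "The CWRT will be terminated before volitional symptom limitation if" SpO2 falls below 78%.

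The Statistical analysis section gives one model for every outcome of this type: "Continuous outcome variables will be analysed using linear mixed models, controlling for recruitment site and baseline values as required". The analysis set is equally general: "All data will be analysed by intention to treat, with inclusion of all available data regardless of whether the intervention is completed". Neither sentence mentions tests ended by the SpO2 rule.

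The Sample size section plans for 61 per group: "This is based on the intermediate boundary (150 s) of the mean important difference range for the CWRT (SD = 292 s"). It makes no stated allowance for stopped tests.

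Other sections bear on how often the stop might occur. The Background says: "People with fILD tend to experience more severe diffusion limitation, greater exercise induced oxyhaemoglobin desaturation". The Participants section excludes only those whose resting room-air SpO2 is under 85%. Randomisation is stratified by whether SpO2 falls below 90% on the room-air 6-minute walk test, but the Statistical analysis section does not name that stratum as a covariate.

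**The concern.** A test that ends because the participant can no longer continue measures endurance. A test ended by the assessor at the SpO2 limit shows only that symptom-limited endurance was at least that long. A linear model applied to both kinds of time gives them the same meaning.

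Take a participant whose leg-muscle endurance improves but who still reaches the SpO2 limit at the same minute. That person contributes no change, whatever the true gain. The article's own rationale makes this pattern plausible. The Background expects interval training to act on peripheral muscle without overloading the cardiorespiratory system, and it attributes desaturation to gas-exchange and vascular impairment.

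The stake is how a small or null difference is read. The Discussion says the findings will show whether HIIT is equivalent or superior to MICT. Without the reasons for stopping, a difference reduced by truncation could not be told apart from a true absence of benefit.

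**Working it through.** **1. The plan's own figure.** Inputs from the Sample size section: difference 150 s, SD 292 s, two-sided 5%, power 80%.

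- Standard error with 61 per group: 292 × √(2/61) = 52.9 s.
- 150 / 52.9 = 2.84.
- Power is 80.4% by the noncentral t and 81.0% by the normal approximation.
- The smallest group size reaching 80% by the t calculation is 61, so the stated 122 is reproduced.

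There is little reserve. 122 / 0.95 = 128.4, or 129, so the 130 to be randomised covers the 5% attrition expected at the end of training and little else.

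**2. Simple dilution (illustrative).** Let p be the share of participants whose stopped tests show no treatment difference. The documents do not give p. The observed difference is 150 × (1 − p), with the SD held at 292 s and 61 per group.

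| p | Difference | Power (t) | Power (normal) |
|---|---|---|---|
| 0 | 150 s | 80.4% | 81.0% |
| 5% | 142.5 s | 76.2% | 76.9% |
| 10% | 135 s | 71.7% | 72.4% |
| 20% | 120 s | 61.5% | 62.2% |
| 30% | 105 s | 50.4% | 51.0% |

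**3. Relaxing the dilution assumptions.** Suppose 20% are affected, their tests keep half the effect, and their change has a quarter of the planning SD (73 s).

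- Difference: 0.8 × 150 + 0.2 × 75 = 135 s.
- Variance in MICT: 0.8 × 292² + 0.2 × 73² = 69,277.
- Variance in HIIT: 69,277 + 0.2 × 0.8 × 75² = 70,177.
- Pooled SD: √69,727 = 264 s.
- Power (normal): 80.6%.

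Under these inputs almost nothing is lost, because early stops also narrow the spread of the outcome.

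**4. Does the direction hold?** A simulation used 61 per group, 1,500 trials per setting, and analysis of covariance on the observed baseline time. All inputs except 150 s and 292 s are assumptions:

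- Baseline symptom-limited time was log-normal (median 270 s, log-SD 0.5).
- Change was normal with mean 100 s and SD 292 s, plus 150 s in HIIT, with times floored at 20 s.
- A share of participants was desaturation-prone, with a baseline stop at 50–100% of their symptom-limited time.
- The follow-up stop moved by a random amount (SD 60 s), plus any delay due to HIIT.
- The observed time was the earlier of the two.

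With no stops the estimate was about 137 s; the floor keeps it below 150 s.

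| Prone share | HIIT delays desaturation by 0 s | by 150 s | by 300 s |
|---|---|---|---|
| 10% | 126 s, power 73% | 137 s, 82% | 148 s, 86% |
| 20% | 113 s, power 67% | 137 s, 83% | 156 s, 92% |
| 40% | 90 s, power 54% | 137 s, 90% | 177 s, 99% |

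The estimate is attenuated with no delay, unaffected at 150 s, and inflated at 300 s.

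**5. Is a censored model a safe replacement?** In simulations with desaturation time independent of endurance, true difference 150 s and 15–35% of tests stopped, a Tobit model returned 148–150 s. With a correlation of 0.6 between desaturation time and endurance and no delay, it returned 166 s. It recovers the target only when its own assumption holds.

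**The case against.** The strongest objection is that the article does not say symptom-limited time is the target. It defines endurance time on a standardised test and states the SpO2 stop as part of that test. Time to any protocol-defined stop is a legitimate outcome, and for that quantity nothing is censored and randomisation protects the comparison. This stands. The Primary outcome section can be read either way, which is why the target needs stating.

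A reader might infer that the primary difference is biased towards zero and that the 80% power is lost. The documents do not support that. They give no stop rate, they do not say whether training shifts the time to desaturation, and they do not say whether the 150 s and 292 s came from tests with a similar stop. If those figures did come from such tests, some attenuation is already in the planning values.

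A reader might also infer that stopped tests will be scored as if completed. The article does not say so. Detailed handling may sit in an analysis plan that is not shown, and its absence from a condensed article is not the finding.

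Stratifying on walk-test desaturation helps to balance prone participants between arms. It does not restore information lost when a test is cut short, and the stratum is not named in the model.

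**Conclusion.** The point holds in conditional form. The article sets a stop that, in its own words, comes before symptom limitation. It names one linear model that does not separate such stops, and it leaves open which of two quantities is primary. If symptom-limited endurance is meant, the HIIT–MICT difference can be attenuated when stops are frequent and insensitive to training.

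The size cannot be derived from the documents. The dilution figures show what is possible, and they rest on an assumed share affected, no effect in stopped tests and an unchanged SD. The loss can be nil if stopped tests keep part of the effect with a smaller spread, and it can reverse if HIIT delays desaturation.

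Replacing the primary model with a censored one is not justified, since that swaps one unverified assumption for another. The remaining changes are cheap and worth making, because they allow a null result to be checked for truncation.

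**What to change.** Leave the stopping rule unchanged and keep the linear mixed model as the primary analysis. Then:

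1. State whether the primary quantity is time to any protocol-defined stop or symptom-limited time.
2. Record the reason for stopping at every CWRT, including baseline, because baseline tests are subject to the same rule.
3. Report the number of SpO2-stopped tests by arm and visit.
4. Add the SpO2 randomisation stratum (6-minute walk test below 90%, or 90% and above) as a covariate in the linear mixed model.
5. Prespecify a sensitivity analysis that treats SpO2-stopped times as right-censored, by a Tobit or time-to-event model. State its assumption that desaturation time is unrelated to latent endurance given the covariates. A Tobit model for follow-up times does not by itself handle a baseline time that was also cut short, so say how that is treated.

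The cost is one case report form field, if it is not already captured, and one extra model. The sample size need not change on this ground, because the documents give no stop rate on which to base a revision.
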